#### **6.4 Recruitment and selection of participants\***

The randomised controlled trial will include six lecturers and six classes (20 to 50 students each class or  $n=300$ ). There are two recruitment processes in this RCT including the lecturer and students. The lecturer will be included in the RCT if he/she meets the following inclusion criteria: 1) run two classes of the physical education course; 2) willing to take part in lecturer training before the physical education course class begins; and 3) willing to invite their students to take part in the pilot study. The chief investigator A/[name] will be sending the recruitment to applicable members of staff at Universitas Pendidikan Indonesia especially lecturers who run the elective physical education course.

The chief investigator A/[name] will be sending the recruitment letter to students enrolled in a physical education course via the participating lecturers (and consenting). Participation in this RCT is voluntary, and all participants will be given Participant Information Statements and invited to sign a Participant Consent Form to participate. Participation or non-participation in this study will not affect students' scores in physical education courses. The number of students in each class varies from 20-50 students. Students will be included in the RCT if they meet the following inclusion criteria: 1) students enrolled in a physical education course with a lecturer who will participate in the pilot study; 2) voluntarily participate in the RCT; and 3) owns an android smartphone. The six lecturers who agree to participate will be randomly assigned to intervention or control. Participation in this RCT is voluntary, and all lecturers and students will be given Participant Information Statements and be invited to sign a Participant Consent Form to participate.

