| BLINDING/MASKING       | The lecturers (n=6) will not be blinded as those randomly assigned to the intervention group (n=3) will be involved in professional development before they implement the intervention.                                                                                                                                                                                                                                                                                                                                                                                                                                                                                                                                                                                                        |
| OUTCOMES               | Primary outcome: Difference in students' physical activity levels, knowledge and motivation at post-test (at the completion of a 16-week semester) compared with the control group.
Secondary outcome: Student's experience and enjoyment of the technology-supported physical education course.                                                                                                                                                                                                                                                                                                                                                                                                                                                                                           |
| STUDY DURATION         | 16 weeks.                                                                                                                                                                                                                                                                                                                                                                                                                                                                                                                                                                                                                                                                                                                                                                                      |

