### 6.2 Sample size including power calculation

The sample size calculation is based on the difference in change in the primary outcome (physical activity) from pre- to post-intervention in both group (intervention and control group). Based on previous studies on technology-based physical activity interventions in university students, mean effect sizes of around  $d = 0.5$  are expected in analyses. To detect such intervention effects in two-sided significance testing ( $\alpha = .05$ ) with a power of 80%, a sample size of 128 participants is required. Taking into account an expected study drop-out of about 20%, 150 participants must be included in the study and participants response rate of about 50%, hence, 300 students (six classes of physical education course) will be invited.

Number of Participants

N=6 physical education course lecturers

(a) n=3 will be assigned to the intervention group,

(b) n=3 will be assigned to the control group.

n=300 students will be randomised 1:1 to either an intervention arm

(a) n=150 a technology-supported physical education course (intervention group)

(b) n=150 non-technology-supported physical education course (control group).

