## 6.6 Intervention

The six lecturers who agree to participate will be randomly assigned to intervention or control and will be asked to invite the students who enrol in their physical education course. The intervention lecturer will have lecturer training and implement the technology-supported physical education course for one semester (16 weeks). The outcome will be assessed at pre-test (1st week of physical education course after students agree to participate) and post-test (last week of the physical education course). Students will also be invited to participate in a focus group about their experience using the technology at the end of the course. The intervention group will receive 16 weeks of the physical education course incorporated with a modified prototype.

The type of technology that will be utilised in the RCT is a lecturer site and a student's mobile app that incorporated the physical education course at a university setting. The lecturers' website is entitled PESSPA (Physical Education Supporting Site for Physical Activity), while the student's app is entitled PESAPA (Physical Education Supporting App for Physical Activity). The PESSPA includes the following features (1) Learning management system features such as uploading course materials (text, pdf, picture, video, direct link), creating quizzes, creating assignments, creating discussions for every lesson week (2). Reviewing students goal settings, physical fitness test results, dietary and physical activity records; and (3). Uploading exercise examples and exercise video guidelines. The PESAPA includes the following features: (1) Access course materials (informative texts, pdfs, pictures, videos, etc.), quizzes, assignments submission, and weekly discussions; (2) goal settings opportunities, physical fitness testing protocols, dietary and physical activity recording opportunities; and (3). Access exercise examples and exercise video guidelines.

Figure 1 shows the screenshot of the PESSPA where lecturers are able to manage their physical education course such as adding text, adding file resources, embedding file from google drive and embedding video from youtube. Course material uploaded by lecturers can be access by students via PESAPA (see Figure 2). These figures only show one of the PESSPA and PESAPA feature interpreted the initial design principle one.

[figure not shown]

Figure 1. Screenshot of learning management system features on PESSPA.

[figure not shown]

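### Section 6.4 asks for two classes per lecturer but counts six classes for six lecturers, and nothing fixes the study class before unblinded lecturers are allocated

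*Protocol*

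**What the plan says.** **Number of classes.** The first lecturer criterion in section 6.4 is to "run two classes of the physical education course". The same section says the trial "will include six lecturers and six classes". Section 6.2 uses the same count: "300 students (six classes of physical education course) will be invited". On class size, section 6.4 states: "The number of students in each class varies from 20-50 students".

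**Who is eligible and who invites.** Under the student criteria in 6.4, anyone enrolled with a participating lecturer qualifies, subject to consent and owning an Android phone. That covers both of a lecturer's classes. Under 6.6 the lecturers are first assigned to an arm and then "will be asked to invite the students who enrol in their physical education course". Sections 6.4 and 6.5 also route the invitation through the lecturers.

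**Timing and blinding.** Section 11 places lecturer training in the second half of August 2022 and student recruitment in September 2022. Only intervention lecturers are trained, so allocation comes before any student is approached. The synopsis states: "The lecturers (n=6) will not be blinded".

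**Change of class.** Section 6.5 provides that if few students agree, with 30 given as the limit, the lecturer invites students from a further physical education class. It does not say which class, or whether the limit applies to one class or to the whole trial.

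**The concern.** The two counts in section 6.4 do not agree, and the gap concerns which clusters enter the trial. If six classes are used out of 12 or more eligible ones, about half are left out by a rule that the protocol does not state.

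Randomising lecturers balances the lecturers. It does not protect a choice between a lecturer's classes that is made once the arm is known. If that choice is made differently in the two arms, for example by size, convenience or apparent interest, the student groups differ for reasons unrelated to the app. This happens before any student is asked for consent, so it is separate from who agrees within a class. Which classes enter is a recruitment rule that belongs in the protocol, not a detail to be left to an analysis plan.

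**Working it through.** **Inputs from the protocol.** Six lecturers and six classes (6.2, 6.4); two classes per lecturer (6.4); 20 to 50 students per class (6.4); 300 invited and 150 to be included (6.2); "participants response rate of about 50" per cent (6.2); limit of 30 (6.5).

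**1. The plan's own figure.** Invitations = participants to include / response rate = 150 / 0.50 = 300. This reproduces the stated 300.

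**2. Class count.** Lecturers x classes per lecturer = 6 x 2 = 12, against six stated.

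**3. Students available and expected consents at 50%.**

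| Classes | Students (20 to 50 each) | Consents at 50% | Mean class size needed for 300 |
|---|---|---|---|
| 6 | 120 to 300 | 60 to 150 | 300 / 6 = 50 |
| 12 | 240 to 600 | 120 to 300 | 300 / 12 = 25 |

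Six classes reach 300 only if every one is at the maximum of 50. Twelve classes reach it at a mean size of 25, well inside the stated range. The figure of 300 therefore does not settle which count was meant.

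**4. How often the rule in 6.5 would apply.**
- *Head count per class.* Expected consents are 0.50 x 20 = 10 up to 0.50 x 50 = 25, always below 30. If each student agrees independently with probability 0.5, the chance of 30 or more consents is about 0.001 in a class of 40 and about 0.10 in a class of 50. A further class would be the usual outcome.
- *Head count for the whole trial.* The expectation is 150 consents from 300 invitations, so a limit of 30 would hardly ever be met.
- *Percentage.* The sentence speaks of a proportion but gives 30 without a unit. If 30% was meant, a class responding at 50% would not trigger the rule.

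**5. Order of events.** Sections 6.6 and 11 and the synopsis together give this order: lecturers are allocated, intervention lecturers are trained, then unblinded lecturers invite students. No section places the naming of the study class, or of the further class under 6.5, before allocation.

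**The case against.** A reader might infer that an unblinded lecturer picks the better of two classes. The documents do not say so for the initial class. Section 6.6 can be read as inviting everyone in the lecturer's course. Under 6.4 the chief investigator issues the recruitment letter, so the trial team could name the class. The class could also be settled when the lecturer is recruited. The two-class criterion may simply provide one study class and one reserve for 6.5. All of this stands: the text supports that the class is not fixed, not that the lecturer chooses it. Only the further class in 6.5 is expressly brought in by the lecturer.

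Motive is not documented either. According to 6.1 the university system enrols students at random, and the pre-test falls in week 1, so lecturers may know little about their classes when they invite. That lowers the likely bias. It does not make a later choice between two formed classes random, since size and convenience are visible from the start.

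A reader might also want to put a number on the bias. With assumed between-class variance shares of 0.02 to 0.10, the better of two classes exceeds their average by 0.564 x sqrt(share), which is 0.08 to 0.18 SD. The documents give no such share. The formula also supposes that every intervention lecturer identifies the better class without error and that no control lecturer tries to. The result is a shift in level before pre-test adjustment, whereas the planned d = 0.5 in 6.2 refers to change from pre-test to post-test. Expressing the shift as a percentage of 0.5 is therefore not supported. If classes are chosen arbitrarily in both arms, the expected bias is zero.

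**Conclusion.** The mismatch is real. The two-class criterion implies 12 classes, six are counted, and on either reading some text has to change: if both classes are invited the count is wrong, and if only one is used the rule for choosing it is missing. Because unblinded lecturers invite students after allocation, and 6.5 has them add a class with no rule for which one, the plan leaves room for selection that differs by arm.

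The size of any bias cannot be derived from the documents. The analysis in 6.3 takes pre-test data as a covariate, which would remove the part that shows in measured baseline values but not necessarily differences in expected response to the course. How often 6.5 would apply depends on whether its limit is a head count per class, a head count overall or a percentage. This is an inexpensive improvement worth making, not evidence that the comparison is biased.

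**What to change.** **Main option.** Before the six lecturers are randomised, the trial team lists both classes of each lecturer, draws one at random as the study class and records the other as the reserve. Section 6.5 is amended so that only that reserve may be called on, and so that the limit of 30 has a unit and a level (per class or overall). Sections 6.2 and 6.4 state that six of 12 classes are used, with the reserves named. Section 6.2 should also acknowledge that six classes supply 300 invitations only when all are full.

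**Alternative.** Enter both classes of every lecturer from the start and change the count to 12 classes (240 to 600 students). This removes the choice altogether. It may be the simpler course if the limit in 6.5 is a head count per class, since most reserves would then be called on anyway.

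**Cost.** The main option needs a six-line random draw and changes of wording, and lecturers lose any say in which class takes part. The alternative adds online questionnaires and app accounts but needs no further lecturers.

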#### **6.5 Informed consent process**

The researcher is a current academic staff member at Universitas Pendidikan Indonesia where the study will be conducted, although he is currently on study leave while he is conducting the study. Participation in this study is voluntary. As per the approved pilot study (Project No.: 2021/071), to recruit the course lecturers, the researcher will ask the course coordinator to send an email to course lecturers inviting them to participate in the study. Again, following the approved recruitment processes for the pilot study, the researcher will also ask the consenting course lecturers to invite students who are enrolled in the physical education course to participate in the study. The email will attach the RCT participant information statement and the link to the online RCT consent form. The students who consent to participate in the study will be asked to sign the online RCT consent form. The consent form and the participant information statement will provide the appropriate contact details for those interested in participating. The course lecturers and students who do not consent will not be disadvantaged in any way. Their marks/grades will not be affected nor will their relationship

with the researcher or Universities be affected. If only a small proportion of students agree to participate in the study (i.e., less than 30), the course lecturer will invite students from another physical education class to participate in the study.

Participants will provide written consent to be involved in the RCT (via a RCT consent form). One of the data collection methods is participation in a focus group discussion where they will be asked to provide to oral consent before participating.

## 6.6 Intervention

The six lecturers who agree to participate will be randomly assigned to intervention or control and will be asked to invite the students who enrol in their physical education course. The intervention lecturer will have lecturer training and implement the technology-supported physical education course for one semester (16 weeks). The outcome will be assessed at pre-test (1st week of physical education course after students agree to participate) and post-test (last week of the physical education course). Students will also be invited to participate in a focus group about their experience using the technology at the end of the course. The intervention group will receive 16 weeks of the physical education course incorporated with a modified prototype.

The type of technology that will be utilised in the RCT is a lecturer site and a student's mobile app that incorporated the physical education course at a university setting. The lecturers' website is entitled PESSPA (Physical Education Supporting Site for Physical Activity), while the student's app is entitled PESAPA (Physical Education Supporting App for Physical Activity). The PESSPA includes the following features (1) Learning management system features such as uploading course materials (text, pdf, picture, video, direct link), creating quizzes, creating assignments, creating discussions for every lesson week (2). Reviewing students goal settings, physical fitness test results, dietary and physical activity records; and (3). Uploading exercise examples and exercise video guidelines. The PESAPA includes the following features: (1) Access course materials (informative texts, pdfs, pictures, videos, etc.), quizzes, assignments submission, and weekly discussions; (2) goal settings opportunities, physical fitness testing protocols, dietary and physical activity recording opportunities; and (3). Access exercise examples and exercise video guidelines.

Figure 1 shows the screenshot of the PESSPA where lecturers are able to manage their physical education course such as adding text, adding file resources, embedding file from google drive and embedding video from youtube. Course material uploaded by lecturers can be access by students via PESAPA (see Figure 2). These figures only show one of the PESSPA and PESAPA feature interpreted the initial design principle one.

[figure not shown]

Figure 1. Screenshot of learning management system features on PESSPA.

[figure not shown]

Figure 2. Screenshot of learning management system features on PESAPA.

Table 1. Course content for intervention and control group

| Week | Intervention Group                                 | Control Group                                      |
|-------------|-----------------------------------------------------------|-----------------------------------------------------------|
| 1           | Course Introduction                                       | Course Introduction                                       |
| 2           | Physical activity, Healthy and active lifestyle knowledge | Physical activity, Healthy and active lifestyle knowledge |
| 3           | Health-related physical fitness knowledge                 | Health-related physical fitness knowledge                 |
| 4           | Goal setting in Physical activity and fitness             | Goal setting in Physical activity and fitness             |
| 5           | Body composition                                          | Body composition                                          |
| 6           | Aerobic fitness                                           | Aerobic fitness                                           |
| 7           | Muscular fitness and flexibility                          | Muscular fitness and flexibility                          |
| 8           | Midsemester exam                                          | Midsemester exam                                          |
| 9           | Nutrition: Healthy eating                                 | Nutrition: Healthy eating                                 |
| 10          | Aerobic activity- aerobic dance                           | Aerobic activity- aerobic dance                           |
| 11          | Aerobic activity- GPS-Based activity                      | Aerobic activity- GPS-Based activity                      |
| 12          | Muscular strengthening                                    | Muscular strengthening                                    |
| 13          | Flexibility training                                      | Flexibility training                                      |
| 14          | Create an individual fitness training                     | Create an individual fitness training                     |
| 15          | Overcome physical activity barrier                        | Overcome physical activity barrier                        |
| 16          | Final exam                                                | Final exam                                                |

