## 11. TIMELINES / MILESTONES

Predictive timeline for this study:

- Lecturer's recruitment first half of August 2022
- Lecturers training second half of August 2022
- Student's recruitment September 2022
- Pre-test September 2022
- Intervention September 2022 to January 2023
- Post-test January 2023
- Data Analysis January to February 2023
- Publication March 2023

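### Student consent is sought through unblinded lecturers after they have been allocated, and the arm is not withheld until consent and pre-test are complete, so who consents can differ by arm

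*Protocol*

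**What the plan says.** The steps are spread over several sections of the protocol.

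- **Allocation, then invitation.** Section 6.6 has six lecturers who "will be randomly assigned to intervention or control and will be asked to invite the students" enrolled in their course.
- **Dates.** Section 11 lists "Lecturers training second half of August 2022" and then "Student's recruitment September 2022". It gives no date for the randomisation itself. The Synopsis and Sections 6.1 and 6.6 describe training for the intervention lecturers only, so allocation must be known by the time training takes place.
- **Blinding.** The Synopsis states: "The lecturers (n=6) will not be blinded as those randomly assigned to the intervention group (n=3) will be involved in professional development".
- **Route of invitation.** Under Section 6.5 "the researcher will also ask the consenting course lecturers to invite students who are enrolled in the physical education course". Section 6.4 has the chief investigator's letter reach students through the lecturers, and makes willingness to invite students the third lecturer inclusion criterion.
- **Uptake.** Section 6.2 plans on a "participants response rate of about 50" per cent.
- **Baseline.** Section 6.6 places the pre-test in week 1, once the student has agreed to take part.
- **Top-up.** Under Section 6.5, if fewer than 30 students agree, the course lecturer invites students from another class.
- **Safeguards.** Section 6.1 says that the university system enrols students with lecturers at random. Section 6.5 provides an information statement and an online consent form. Section 6.3 uses the pre-test as a covariate and adjusts for variables that differ significantly between groups.

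**The concern.** The trial allocates lecturers and then recruits students through people who know the allocation. Randomising six lecturers, and enrolling students with them at random, makes the invited groups comparable in expectation. It does not do the same for the students who accept. If the prospect of an app, or the enthusiasm of a newly trained lecturer, attracts a different kind of student from the usual class, the analysed groups differ before the course has any effect.

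The selection could bear directly on the outcomes. Section 3 treats motivation as a determinant of physical activity, and motivation is itself one of the three outcomes named as primary. A larger sample does not remove this kind of bias, and analysis removes only the part that the measured pre-test carries. Students who decline have no pre-test, so the selection cannot be examined afterwards on the trial's own measures.

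**Working it through.** **The plan's own figures.** For d = 0.5, two-sided alpha 0.05 and 80% power, the normal approximation is 2 × (1.96 + 0.84)² / 0.5² = 62.7, so 63 per arm. The t-test calculation gives 63.77, so 64 per arm and 128 in total, which agrees with Section 6.2. At 50% response, 300 × 0.5 = 150 consent and 150 decline or do not answer.

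**Room for selection.** Half of the invited students select themselves after their lecturer knows the arm. The document gives no consent rates by arm and no link between willingness and outcome. Everything below is therefore an assumption.

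**Shift before adjustment.** If a share p consents and consenters differ from non-consenters by g, the consenters' mean differs from that of the whole class by (1 − p) × g. With p = 0.5, g = 0.3 SD in the app arm and g = 0 in control:

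(1 − 0.5) × 0.3 = 0.15 SD.

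**Shift after the planned adjustment.** With the pre-test as covariate and equal variances at both visits, the adjusted difference is D_post − r × D_pre, where r is the pre-post correlation.

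- Shift equal at both visits: 0.15 × (1 − r). For r = 0.8 this is 0.03 SD; for r = 0.5 it is 0.075 SD.
- Shift only in what drives change, so that D_pre = 0: all 0.15 SD remains.

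**Other assumptions.** Let willingness be normal and correlate rho with the outcome. The mean shift among consenters is rho × φ(c)/p, where c is the consent threshold. All differences in this table are before adjustment.

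| Consent in the two arms | rho | Spurious difference (SD) |
|---|---|---|
| 60% v 40% | 0.1 / 0.3 / 0.5, same in both arms | 0.03 / 0.10 / 0.16 |
| 70% v 30% | 0.1 / 0.3 / 0.5, same in both arms | 0.07 / 0.20 / 0.33 |
| 50% v 50% | 0.3 in one arm, 0 in the other | 0.24 |

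In the first two rows the arm with the lower consent has the higher mean, so the bias can go either way. The last row shows that equal consent rates do not rule bias out. If that shift is equal at both visits, 0.24 × (1 − r) leaves 0.12 SD (r = 0.5) to 0.05 SD (r = 0.8).

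**Would the baseline tests catch it?** Section 6.3 adjusts for other variables only if they differ significantly. With 75 consenters per arm the standard error is √(2/75) = 0.163 SD, so an imbalance of 0.15 SD has z = 0.15/0.163 = 0.92. It would reach p < 0.05 about 15% of the time, ignoring clustering.

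**The top-up rule.** Section 6.4 gives classes of 20 to 50 students. At 50% response that is 10 to 25 consenters per class, always below 30. If the threshold applies per class, the second round would be routine. If it applies to the whole study (150 expected), it would be rare. The text does not say which. In either case the person inviting knows the arm.

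**The case against.** The strongest reply is that the plan has safeguards. The letter comes from the chief investigator, and the email carries an information statement and a link to an online consent form. No section lets a lecturer choose whom to invite within a class. Grades are unaffected, enrolment with lecturers is random, and the pre-test is a covariate. This stands: a reader might infer that the plan does nothing against the risk, and that would be wrong. But these measures standardise the content of the invitation and correct measured imbalance. None keeps the arm from students until consent and pre-test are complete.

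A reader might also infer that the invitation tells students their arm, or that consent will in fact differ. The document does not show either. The consent material is not in the copy reviewed, so it cannot be judged whether the information statement is neutral. The protocol also does not say that app access depends on consent. Nor are all six lecturers described as trained before they invite students; that applies to the intervention lecturers.

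It is tempting to set 0.15 SD against d = 0.5 and say that 30% of the planned effect could be spurious. That is not supported. The 0.15 is one assumed scenario before adjustment, Section 6.2 defines its effect on the difference in change, and the planned model conditions on the pre-test.

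Finally, the Synopsis and Section 6.2 say that 300 students are randomised 1:1. Individual randomisation after consent would remove the problem, but Sections 6.1, 6.4 and 6.6 describe allocation of lecturers, with students following their lecturer.

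**Conclusion.** The concern holds as a risk that the protocol's own order of recruitment creates: allocation first, then invitation through unblinded lecturers, then consent by about half, then pre-test. Random enrolment does not protect against differential consent, and the existing safeguards are partial. The top-up rule adds a second recruitment step by someone who knows the arm.

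The size cannot be derived from the document. In the main illustration (a 0.3 SD gap in the app arm only, 50% consent) the shift is 0.15 SD before adjustment. About 0.03 to 0.08 SD remains after it if the shift is equal at both visits and the pre-post correlation lies between 0.8 and 0.5. More remains if selection acts on drivers of change that the pre-test does not measure. The direction is not known either. Because the change is cheap and the analysis cannot fully repair the problem later, recruitment should be amended before students are invited.

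**What to change.** Amend Sections 6.4 to 6.6 as follows.

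1. The course coordinator, who already emails the lecturers, sends one identical REDCap invitation, information statement and pre-test to all enrolled students of the six study classes. The text describes both formats without saying which one the class follows. The limit to six classes matters: each lecturer must run two, so inviting all their students would cover twelve classes rather than the six planned.
2. Consent and pre-test close in week 1, before the class format is announced or app access is issued. Week 1 is the course introduction in both arms and already holds the pre-test.
3. Any reserve class for the top-up is named before allocation and recruited in the same way. State whether the threshold of 30 applies per class or to the study.
4. The third lecturer inclusion criterion is changed, since lecturers no longer invite students.
5. Numbers enrolled, invited and consented are reported by lecturer and arm.

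**Cost.** A minor ethics amendment, because Section 6.5 follows an approved recruitment process; no new staff or system. Response may fall somewhat without the lecturers' encouragement, and there is little slack: 300 × 0.5 × 0.8 = 120 evaluable students, already below 128. At an assumed 40% response, 300 × 0.4 × 0.8 = 96 would remain, so response should be monitored centrally.
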